## Abstract

**Background:**

Despite almost 30 years of effective chemotherapy with MDT, the global new case detection rate of leprosy has remained quite constant over the past years. New tools and methodologies are necessary to interrupt the transmission of *M. leprae*. Single-dose rifampicin (SDR) has been shown to prevent 57% of incident cases of leprosy in the first two years, when given to contacts of newly diagnosed cases. Immunization of contacts with BCG has been less well documented, but appears to have a preventive effect lasting up to 9 years. However, one major disadvantage is the occurrence of excess cases within the first year after immunization. The objective of this study is to examine the effect of chemoprophylaxis with SDR and immunoprophylaxis with BCG on the clinical outcome as well as on host immune responses and gene expression profiles in contacts of newly diagnosed leprosy patients. We hypothesize that the effects of both interventions may be complementary, causing the combined preventive outcome to be significant and long-lasting.

**Methods/design:**

Through a cluster randomized controlled trial we compare immunization with BCG alone with BCG plus SDR in contacts of new leprosy cases. Contact groups of around 15 persons will be established for each of the 1300 leprosy patients included in the trial, resulting in approximately 20,000 contacts in total. BCG will be administered to the intervention group followed by SDR, 2 months later. The control group will receive BCG only. In total 10,000 contacts will be included in both intervention arms over a 2-year period. Follow-up will take place one year as well as two years after intake. The primary outcome is the occurrence of clinical leprosy within two years. Simultaneously with vaccination and SDR, blood samples for *in vitro* analyses will be obtained from 300 contacts participating in the trial to determine the effect of these chemo- and immunoprophylactic interventions on immune and genetic host parameters.

**Discussion:**

Combined chemoprophylaxis and immunoprophylaxis is potentially a very powerful and innovative tool aimed at contacts of leprosy patients that could reduce the transmission of *M. leprae* markedly. The trial intends to substantiate this potential preventive effect. Evaluation of immune and genetic biomarker profiles will allow identification of pathogenic versus (BCG-induced) protective host biomarkers and could lead to effective prophylactic interventions for leprosy using optimized tools for identification of individuals who are most at risk of developing disease.

**Trial registration:**

Netherlands Trial Register: NTR3087

## Background

The global number of new leprosy cases has remained constant over the past years [1], indicating that transmission of *Mycobacterium leprae,* the causative agent of leprosy, is ongoing in many endemic countries. The basic intervention is multidrug therapy (MDT) given to newly found leprosy cases, but this seems to be insufficient to decrease the number of new cases.

The main risk of exposure to *M. leprae* is in close contacts of new, untreated cases. Epidemiological studies have shown that the chance of finding a previously undiagnosed leprosy patient is ten times higher in household contacts of leprosy patients than in the general population, and the chance of finding leprosy among different categories of neighbors and social contacts is between three and five-fold [2,3]. Therefore, it has been suggested that contacts should be the main focus of a future leprosy control strategy. Such strategy should have three basic pillars: 1) case detection; 2) case management; and 3) contact management [4].

In the past years, many studies have investigated the use of immunoprophylaxis (vaccination) and chemoprophylaxis to prevent leprosy. These interventions have focused primarily on contacts of leprosy patients. Bacillus Calmette-Guérin (BCG) vaccination is known as a vaccine against tuberculosis and is routinely given to infants as part of the neonatal immunization scheme in many parts of the world. BCG is also recognized as protecting against leprosy [5,6]. Over the years several vaccine trials using BCG have been performed to establish its protective effect against leprosy, often in combination with *M. leprae* or related mycobacterium vaccines. BCG was as good as, or superior to the other mycobacterium vaccines [4].

BCG efficacy appeared to be significantly higher in studies when BCG vaccination was targeting household contacts of leprosy patients compared with the ones conducted in the general population: 68% *vs.* 53% [5]. In Brazil, the government officially recommends BCG (re)vaccination to protect household contacts of leprosy cases. This policy was assessed in a cohort study showing that the protection conferred by BCG was 56% and was not substantially affected by previous BCG vaccination [7]. The risk of tuberculoid leprosy during the initial months was high among those vaccinated with no previous BCG vaccination; 21 of 58 new leprosy cases (36%) occurred in the first year. This risk, however, had substantially declined by the first year and in the following years the protection rate in this group reached 80% [7]. The results of this study are not conclusive due to some methodological inconsistencies. In particular, the issue of increased risk of tuberculoid leprosy in the first months after BCG vaccination needs further evaluation.

With regard to chemoprophylaxis, the COLEP study in Bangladesh showed that the use of a single dose of rifampicin (SDR) in contacts of newly diagnosed leprosy patients reduced the overall incidence of leprosy in the first two years with 57% [8]. Furthermore, this study showed that the effect of SDR depended on the BCG status of the contact [9]: If the contact had received BCG vaccination as part of a childhood vaccination program (as established by the presence of a BCG-scar), the protective effect of SDR was 80%. Childhood BCG vaccination and SDR each have a protective effect in contacts of approximately 60%, but if contacts who had previously received BCG vaccination also received SDR, the protective effect appeared to be additive.

Based on the experiences with BCG vaccination and SDR chemoprophylaxis in preventing leprosy among contacts of leprosy patients, a trial was initiated in Bangladesh to assess the efficacy of a combined strategy (acronym: MALTALEP study, named after the main sponsor of the research project). The objective of this paper is to describe the design of a cluster randomized controlled trial, in which contacts of newly diagnosed leprosy patients will either receive BCG alone, or BCG plus SDR. In particular, it is important to determine whether the excess cases in the first year after immunoprophylaxis can be prevented by chemoprophylaxis, while maintaining the protective effect.

## Methods/design

### Objectives and hypothesis

The objective of this study is to examine the combined effect of chemoprophylaxis with single dose rifampicin (SDR) and immunoprophylaxis with Bacillus Calmette-Guérin (BCG), in contacts of new cases of leprosy. Both interventions are known to have a preventive effect and we hypothesize that these effects may be complementary, so that the combined effect may be significant and long-lasting.

### Study design

The intervention consists of a cluster randomized controlled trial, with two treatment arms, to study the effectiveness of the BCG vaccine versus BCG in combination with SDR in the prevention of leprosy among contacts of newly diagnosed leprosy patients.

### Setting

The study takes place in the districts of Nilphamari, Rangpur, Thakurgaon and Panchagarh in Northwest Bangladesh. Patients will enter into the trial through the Rural Health Program (RHP) of The Leprosy Mission International Bangladesh (TLMIB), located at the Nilphamari Hospital; a referral hospital specialized in the detection and treatment of leprosy. The population of the four districts is around 7,000,000 (2011 census [10]) and 800–900 new leprosy patients are detected per year. The population in the four districts is mainly rural, but also includes six main towns.

### Participants

Newly diagnosed leprosy patients will be included in the trial after being diagnosed with leprosy according to the Rural Health Program guidelines, which follow those of the National Leprosy Control Program [11,12]. All new leprosy patients are confirmed by a medical officer, and this confirmation is written on the patient card. Around 1,300 consecutive leprosy patients will be enrolled into the study. After a patient is diagnosed, patient details will be recorded (Table 1). Multidrug therapy (MDT) will be started according to the national guidelines. Intake of single-lesion PB (SLPB) patients will be stopped when 500 such patients have been included; the same will apply to the group of other PB patients (PB2-5, with two to five skin lesions on physical examination). This will ensure an intake of at least 300 multibacillary (MB) patients. Within two weeks after the new leprosy patient has received the second dose of MDT (four weeks after the first dose), a survey will be performed among all household contacts. During this survey, contact groups will be formed consisting of approximately 15 persons for each patient. Thus, the total number of contacts included will be around 20,000.

**Table 1 T1:** Patient and contact data recorded

1	Personal data of patient and all selected contacts: name, year of birth, sex and relation of contact to the selected patient
2	Brief information regarding medical history of all contacts (liver disease, malignancies, HIV, TB, leprosy, pregnancy, vaccination status and medication use) to ensure that the participants have no contraindications for BCG vaccination or use of the medicine rifampicin
3	Results of physical examination on signs and symptoms of leprosy (including leprosy classification and WHO disability grade) and actions taken accordingly
4	Interventions: BCG vaccination, medication provided, blood sample taken
5	Record of any adverse reactions and actions taken accordingly
6	Report of follow up visits

Exclusion criteria for patients are as follows: any patient who refuses examination of contacts, any patient who suffers from the pure neural form of leprosy, any patient who resides only temporarily in the study area, any new patient found during contact examination of the index case, any new patient living less than 100 m away from a patient already included in the study or first and second degree relatives of a patient already included in the study.

The following categories of contacts of new leprosy patients have been distinguished for inclusion: those living in the same house (household members), those living in a house on the same compound, sharing the same kitchen, and direct neighbors (first neighbors). Exclusion criteria for contacts are as follows: any person who refuses informed consent, any woman indicating that she is pregnant, any person currently on TB or leprosy treatment, any person below 5 years of age, any person known to suffer from liver disease or jaundice, any person residing temporarily in the area, any person suffering from leprosy at the initial survey (these patients will be referred to the clinic for leprosy treatment) and any person who is a contact of another patient and is already enrolled in the contact group of the other patient.

### Randomization

Each contact group will be randomly allocated to one of the two study arms (Arm 1: BCG only, or Arm 2: BCG plus SDR) by means of computer generation with a 1:1 ratio for each arm. The allocation to receive SDR is stamped on the data collection forms of each contact group. Immunoprophylaxis with BCG will be given at the moment of the contact survey to all included contacts in both arms of the trial, followed by chemoprophylaxis with SDR eight weeks later in contacts of Arm 2.

A schematic representation of the MALTALEP study is given in Figure 1 (left side), together with a non-intervention group (right side) and the sampling framework for analysis of host immune and gene profiles, which is part of the IDEAL study (see below).

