All eligible patients and their contacts will be informed verbally about the study through the reading of the consent form, and then invited to participate. Before inclusion, the patient and their contacts are asked to sign a form if they agree to participate in the study. For illiterate people a thumb print will be taken, and for minors under 16 years of age, the guardian’s additional consent will be taken. Contacts explicitly give consent for BCG vaccination and SDR, and for blood drawing. Furthermore, the researcher has to sign that he/she has accurately read or witnessed the accurate reading of the consent form to the participants, that the individuals have had the opportunity to ask questions and they have given consent freely. Participants will also be informed that they will be offered free consultation and treatment in the case of adverse events following BCG vaccination. They are provided with a vaccination card with details on how to reach the researcher if they have any concerns. Also, participants are informed that their participation is completely voluntary and that they may choose not to participate or stop at any point of time. Their decision not to volunteer, or to refuse to answer particular questions, will not affect their relationship with the researchers or other staff members of RHP.

At the initial contact survey in the patient’s home, BCG will be given to all included contacts, followed by chemoprophylaxis with SDR two months later in those groups randomized to receive it (FU1). Follow-up examinations will be carried out one year (FU2) and two years (FU3) after receiving BCG. The three follow-up moments will be used to investigate whether the contact has developed leprosy or may be a suspected leprosy case (primary outcome measure). These patients will be sent to Nilphamari hospital or a local clinic for further investigation and treatment of leprosy. At these moments both groups will also be examined for adverse events following the BCG vaccination. Blood samples will be taken from 300 randomly chosen contacts for further molecular and immunological testing. Subjects not available for follow-up during the house visits will be contacted in order to plan another house visit. The trial started in July 2012 and will have duration of intake of 24 months. With a total observation period of 2 years after intake, the study will thus be completed after 48 months.

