### Blinding

Ideally, we would like to have set up a (double) blinded trial. However, this was not possible, since we have not been able to locate any company that could produce placebo tablets especially for this trial.

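### The arm is stamped on each contact group's forms and no arm-masked examiner or confirming clinician is described, so knowledge of allocation can bias a diagnosis based on clinical signs; lack of a placebo does not make this unavoidable.

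*Protocol article*

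**What the plan says.** All references are to Methods/design in the protocol article.

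- **Allocation.** Under Randomization, contact groups are allocated "by means of computer generation with a 1:1 ratio for each arm", and "The allocation to receive SDR is stamped on the data collection forms of each contact group". The section does not say when the stamp is applied or by whom.
- **Timing of treatment.** The same section states: "Immunoprophylaxis with BCG will be given at the moment of the contact survey to all included contacts in both arms of the trial". The arms part only at the next step, where BCG is "followed by chemoprophylaxis with SDR eight weeks later in contacts of Arm 2".
- **Intake.** Under Participants: "During this survey, contact groups will be formed consisting of approximately 15 persons for each patient". Contacts are screened at the same survey, and the exclusions include "any person suffering from leprosy at the initial survey".
- **Forms.** Intervention implementation and data collection has staff fill in the data sheets in the field, at clinic visits and contact surveys. Table 1 (Participants) lists examination results, interventions given and follow-up reports among the recorded items.
- **Outcome.** Outcome measures defines the primary outcome as the number of new leprosy patients arising in the contact groups. Intervention implementation and data collection says that FU1, FU2 and FU3 serve to find out "whether the contact has developed leprosy or may be a suspected leprosy case (primary outcome measure"), and that those found go to the hospital or a local clinic. The section on blood samples says that current diagnosis rests on clinical signs.
- **Blinding.** A blinded trial was wanted, but "this was not possible, since we have not been able to locate any company that could produce placebo tablets".

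**The concern.** In an open trial with a laboratory or registry endpoint, a stamped form would matter little. Here the endpoint depends on how carefully someone looks at skin and nerves, and on whether a doubtful sign is called leprosy. An examiner who knows the group received SDR may look less hard, or refer fewer doubtful lesions, without intending to. The opposite could also happen.

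The Blinding section deals only with masking the treatment. Two other safeguards need no placebo: withholding the arm from field staff until they have to act on it, and having cases confirmed by someone who has not been told it. The article describes neither.

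A second, weaker exposure arises at intake. If the stamp is already on the form at the survey, it could influence who makes up the group of about 15, who is asked for consent, and whether a doubtful lesion is called prevalent (excluded) or left to appear later as an incident case.

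**Working it through.** The article gives no figure on this point to reproduce. The check has two parts: the sequence of events, and the size that a bias could reach.

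**1. Sequence**

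| Step | What happens | Is the arm needed? | Is the arm visible? |
|---|---|---|---|
| Survey | Group formed, contacts examined, consent, BCG to all | No, treatment is identical | Unknown: time of stamping not stated |
| FU1 (week 8) | Leprosy examination; SDR in Arm 2 | Yes, for SDR; not for the examination | Yes, if the stamped form is used |
| FU2, FU3 (years 1 and 2) | Leprosy examination and referral | No | Yes, if the stamped form is used; Table 1 also records medication |
| Referral | Hospital or local clinic investigates | No | Not stated to be masked |

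The arm is needed for one action only, the giving of SDR. Up to then the arms have been treated alike, so a difference between arms in cases found at FU1 before dosing could not be an effect of SDR.

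**2. Size (illustration)**

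Inputs from Sample size calculation:
- control rate 4 per 1000 per year, so about 8 per 1000 over two years: p1 = 0.008
- about 10,000 per arm less 10% loss: n = 9,000
- two-sided α = 0.05

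Assumptions, not from the article: SDR has no true effect, and a fraction f of Arm 2 cases goes unrecorded because the arm is known, so p2 = 0.008(1 − f).

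The chance of a significant result favouring SDR is Φ[(d − 1.96·se0)/se1], where
- d = p1 − p2
- se0 = √[2·p̄(1 − p̄)/n], with p̄ = (p1 + p2)/2
- se1 = √[(p1(1 − p1) + p2(1 − p2))/n]

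For f = 0.20: p2 = 0.0064, d = 0.0016, and se0 and se1 are both about 0.00126. The argument is (0.0016 − 1.96 × 0.00126)/0.00126 ≈ −0.69, and Φ ≈ 0.245.

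To allow for clustering, repeat with an assumed design effect of 1.5, that is an effective n of 9,000/1.5 = 6,000. The article gives no design effect.

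| f | Recorded cases, Arm 1 vs Arm 2 (n = 9,000) | Chance, clustering ignored | Chance, design effect 1.5 |
|---|---|---|---|
| 0 | 72 vs 72 | 2.5% | 2.5% |
| 5% | 72 vs 68 | 4.9% | 4.4% |
| 10% | 72 vs 65 | 9.0% | 7.3% |
| 20% | 72 vs 58 | 24.5% | 17.8% |
| 30% | 72 vs 50 | 50.0% | 35.9% |

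For the opposite direction, take the planned 50% effect (0.008 vs 0.004). Power at n = 9,000 is about 93.5% with clustering ignored. If Arm 2 cases are over-recorded by 10% (0.0044), it falls to about 87%.

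**The case against.** **Intake.** A reader might infer that staff do choose and examine contacts with the arm in front of them. The article does not show this. It says that each contact group is allocated and that the forms belong to the group, which fits a stamp applied once the group exists. It refers to detailed research protocols (Preparations and process evaluation), which may settle the timing. Eligible categories and exclusions are also listed, which limits discretion. So exposure at intake is a possibility, left open because the arm is not needed at that stage and the timing is unstated.

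**Suspected cases.** A reader might also infer from the parenthesis in the follow-up text that suspected cases count towards the primary outcome. That reads too much into it. The Abstract and Outcome measures speak of clinical leprosy and new leprosy patients, and the next sentence of the follow-up text sends those found for further investigation. The field visit works as a screen.

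**Confirmation.** Participants says that a medical officer confirms all new leprosy patients. The sentence concerns index patients, but contacts who develop leprosy are referred on for further investigation as well. A confirming step may thus largely exist. It is not stated to be masked, and masked confirmation cannot recover a lesion that an unmasked examiner did not refer.

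**Size.** The percentages rest on assumed under-recording. At 5% the distortion is small, and a moderate bias against SDR would not erase a true 50% effect. This stands: the calculation shows sensitivity and does not predict bias.

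**Partial masking.** Contacts know whether they took SDR and may say so. This is true, and it limits what the fix can achieve.

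The open design is disclosed and an independent monitor visits monthly, but neither is described as keeping the arm from examiners.

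**Conclusion.** The point holds for outcome assessment. The plan places the arm on the forms, rests the primary outcome on clinical signs, describes no masked examiner or confirming clinician, and justifies the open design by a reason that does not rule out either. This is a weakness in a stated procedure and goes beyond missing detail.

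For intake it holds only conditionally: staff may know the arm at the survey, depending on when the stamp is applied.

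Under no true effect, losing about 7 of 72 Arm 2 cases (10%) would raise the chance of a false positive favouring SDR from 2.5% to about 7–9%. Losing 20% would raise it to about 18–24%, and 30% to about 36–50%. The lower end of each range assumes a design effect of 1.5 and the upper end ignores clustering. All of them depend on assumed under-recording rates, and nothing in the article shows that such under-recording will occur.

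**What to change.** 1. State when the stamp is applied. Reveal the allocation only after the group's contact list, baseline examination, consent and BCG are recorded. One way is a sealed envelope per group, opened at FU1 once that visit's leprosy examination is written down. This avoids a call to the trial office or a second visit.
2. Keep the arm and the medication record off the FU2 and FU3 examination forms and the referral slips; hold them on a separate sheet.
3. Count as a primary case only leprosy confirmed at the hospital or clinic to which suspects are already referred, by a clinician not told the arm.
4. Reword the Blinding section to separate the masking of treatment, which a missing placebo prevents, from concealment at intake and masked confirmation, which it does not.

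Cost: reprinted forms, envelopes, and an instruction to the referral clinicians, using the existing visits and referral route. Masking stays partial, because contacts know whether they took SDR.
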